### Further efficacy analysis

Tertiary endpoints will be delineated descriptively and/or tested two-sided in the sense of exploratory data analysis; there will be no alpha correction for these endpoints. The proportions of patients who die will be compared at 6 months after TBI. The estimate of the difference in proportions (Ronopterin versus Placebo), 95% confidence interval and Chi-square *p* value will be calculated. In the case of lower cell frequencies (< 5), the Fisher exact test will be used instead.

Overall survival will be analyzed by log-rank test. Kaplan-Meier estimates of the 25th, 50th and 75th quartiles will be reported. The 95% confidence interval for the median and *p* values will also be calculated.

Absolute values of ICP and CPP (until day 5) will be summarized per treatment group and for each time point by means of descriptive statistics. The 95% confidence intervals will be calculated for the median using non-parametric methods for order statistics.

The comprehensive QOLIBRI assesses health-related quality of life (QoL) within six domains (self-cognition, cognition, daily life and autonomy, social relationships, emotions and physical problems). Total scores in each of these domains of QOLIBRI will be analysed using the *t* test with a two-sided alpha level of 0.05. The mean difference in the scores and the 95% confidence interval under Ronopterin and placebo will be used as the treatment effect estimate.

Partial brain oxygen pressures are recorded every 1 h up to 5 days after the start of the infusion. Absolute values will be summarized per treatment group and for each time point by means of descriptive statistics. The 95% confidence intervals for the mean will be calculated (normal approximation).

The cerebral glucose, lactate, pyruvate and glutamate are recorded every 1 h up to 5 days after the start of the infusion. Absolute values will be summarized per treatment group and for each time point by means of descriptive statistics. The 95% confidence intervals for the mean will be calculated (normal approximation).

The prognostic factor according to Steyerberg et al. [18] predicts the probability of 6-month mortality or probability of 6-month unfavorable outcome. The prognostic factor will be analysed using the *t* test with a two-sided alpha level of 0.05. The mean difference in the score and its 95% confidence interval under Ronopterin and placebo will be summarized for comparability at baseline. A SPIRIT scheme of all study procedures is shown in Fig. 2 (Additional file 1).

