### Randomisation

Patients in the trial treatment are allocated to treatment with Ronopterin or placebo in a ratio of 1:1, via a confidential interactive web response system and block randomisation. Balance in treatment allocation across the study participants is enhanced through stratification by both research site (defined by each participating hospital) and by the age of the patient included (two age groups, 18–39 and 40–60 years).

Patients aged 18–39 years represent the group of patients with generally better recovery perspectives than the group of patients aged 40–60 years. The upper age limit was set to 60 years for safety reasons, as in the NOSTRA phase II trial in particular, elderly patients exhibited renal dysfunction [9].

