### Sample size and power

In the NOSTRA phase II study, an odds ratio for the eGOS of 25.2 in favour of Ronopterin was estimated using ordinal logistic regression with a lower (two-sided) 95% confidence limit of 3.2 [9]. For the sample size estimation in the current NOSTRA phase III study, an odds ratio of 2.3 was assumed, which can be considered as very conservative compared to the preceding estimates. In addition, the following distribution of eGOS relative occurrences across the levels for patients in the placebo group was assumed starting from level 1 to level 8: 0.09, 0.1, 0.1, 0.15, 0.3, 0.25, 0.005 and 0.005. This is a smoothed distribution reflecting the actual distribution in the placebo group in the NOSTRA II study. Sensitivity considerations have shown that the sample size estimation is rather robust against deviations from the aforementioned assumed distribution in the placebo group. In a simpler data situation dichotomized as 50% of the patients on placebo, an odds ratio of 2.3 approximately corresponds to an increase of favourable responses under treatment of 20%.

In the present study eGOS is also the primary parameter of analysis; randomisation was planned in a patient number ratio of 1:1 to achieve maximum statistical power. It was assumed that the treatment effect of Ronopterin compared to placebo would be tested on a two-sided alpha level of 0.05 using the non-parametric Wilcoxon rank-sum test for ordered categorical data. Derived from the NOSTRA phase II trial, the phase II/III trial was designed to detect a treatment effect of an odds ratio of 2.3 (approximately 10-fold lower as in the phase II trial) as statistically significant on an alpha level of 0.05 with statistical power slightly > 90% (92.2%); 220 evaluable patients are needed for the statistical intention-to-treat analysis in the full analysis set (FAS). With this number of 220 patients a lower odds ratio of 2.0 would still be detected with 80% statistical power (alpha = 0.05, two-sided) while a higher odds ratio of 2.6 could be detected with 90% power even at a two-sided alpha level of 0.01. To account for withdrawals and patients lost to follow up, the number of patients to recruit has been increased by 5% to 232 patients.

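### The 6-month mortality test switches from chi-square to Fisher's exact test on an undefined cell count, and it leaves out the age strata that the primary and secondary models include (minor)

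*Protocol article*

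**What the plan says.** All references are to the protocol article.

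- **Test.** Further efficacy analysis, on 6-month deaths: "The estimate of the difference in proportions (Ronopterin versus Placebo), 95% confidence interval and Chi-square *p* value will be calculated". The next sentence is the switch: "In the case of lower cell frequencies (< 5), the Fisher exact test will be used instead". Neither sentence says which kind of count is meant, and neither mentions age.
- **Status.** The same section describes these endpoints as "tested two-sided in the sense of exploratory data analysis; there will be no alpha correction for these endpoints". Secondary outcomes and pre-specified covariates lists mortality among the further endpoints, below the six prioritised secondary ones.
- **Strata.** Randomisation uses "stratification by both research site (defined by each participating hospital) and by the age of the patient included", with age bands 18–39 and 40–60. The primary model (Statistical analysis) and the models under Secondary efficacy analysis all include age band.
- **Planning figures.** Sample size and power gives the placebo eGOS distribution as "starting from level 1 to level 8: 0.09, 0.1, 0.1, 0.15, 0.3, 0.25, 0.005 and 0.005" and states: "For the sample size estimation in the current NOSTRA phase III study, an odds ratio of 2.3 was assumed". It asks for 220 evaluable patients, allocated 1:1.

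**The concern.** A rule that picks the test after the table has been seen should at least have an unambiguous trigger. Here the term can be read in two ways, and the readings part company at the death rates the plan itself assumes.

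If observed counts are meant, the cell that usually falls below 5 is deaths on Ronopterin. The conservative test then applies more often the fewer deaths there are on the drug. The wording appears to replace only the p value, so the risk difference and its interval would stay as they are and could point the other way.

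Separately, mortality would be compared without the age bands that the primary and secondary models include, although the article says that the younger band generally has the better prospects of recovery.

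At stake is the clarity of one exploratory result that will nevertheless be read closely. The primary conclusion is not affected.

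**Working it through.** **Inputs**
- From the document: 110 per arm (220 evaluable, 1:1), placebo level 1 proportion 0.09, odds ratio 2.3, two-sided 0.05.
- Assumptions: eGOS level 1 is death, and the common odds ratio also holds at the death cut.

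**Step 1: reproduce the plan's own figure.** The placebo distribution was shifted by an odds ratio of 2.3 and analysed by a tie-corrected Wilcoxon test (40,000 simulated trials). Power is 92.5%; Whitehead's proportional-odds formula gives 93.1%. The article states 92.2%, so its planning inputs are being read as intended. It states no power for mortality.

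**Step 2: death rate on Ronopterin.** Placebo odds = 0.09/0.91 = 0.0989. Divided by 2.3 this is 0.0430, so the proportion is 0.0430/1.0430 = 0.0412. Expected deaths are 110 × 0.09 = 9.9 and 110 × 0.0412 = 4.5.

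**Step 3: how often the switch occurs.**
- Observed counts: P(Ronopterin deaths ≤ 4) = 0.523 and P(placebo deaths ≤ 4) = 0.026. P(either) = 1 − 0.477 × 0.974 = 0.536.
- Expected counts: with equal arms, the expected deaths per arm are half the total, so the switch needs a total below 10. Its probability is 0.082.

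**Step 4: power and type I error,** by exact enumeration of the two binomials:

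| Rule | Power, 9% vs 4.1% | Type I error, 9% in both arms |
|---|---|---|
| Chi-square throughout | 31.3% | 5.3% |
| Switch on expected counts | 30.8% | 5.3% |
| Switch on observed counts | 25.3% | 4.8% |
| Fisher throughout | 22.6% | 2.9% |

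**Step 5: sensitivity to the placebo death rate** (odds ratio 2.3, 110 per arm). Loss is in percentage points of power against chi-square throughout:

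| Placebo deaths | Switch rate, observed | Loss, observed | Loss, expected |
|---|---|---|---|
| 6% | 86% | 7.2 | 3.6 |
| 9% | 54% | 6.0 | 0.5 |
| 12% | 26% | 2.3 | 0.0 |
| 15% | 10% | 0.4 | 0.0 |
| 20% | 1% | 0.0 | 0.0 |

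At 9% and an odds ratio of 2.0, the observed-count switch rate is 42% (power 19.9% against 24.5%). At the maximum of 330 patients allowed after the interim analysis, with an odds ratio of 2.3, it is 18.7% (power 41.4% against 43.0%).

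**Step 6: p value against interval** (observed-count reading; Wald interval assumed, since no method is named).
- *4 versus 12 deaths.* Difference −8/110 = −7.3 points. Pooled proportion 16/220 = 0.0727; z = 0.0727/√(0.0727 × 0.9273 × 2/110) = 2.08; chi-square p = 0.038. The unpooled standard error is 0.0347, so the 95% interval is −14.1 to −0.5 points. The rule reports Fisher p = 0.066.
- *5 versus 13 deaths.* Same difference, weaker evidence: z = 1.97, chi-square p = 0.049. No cell is below 5, so the rule reports 0.049.

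At the planned effect the reported p value and the Wald interval disagree in 6.0% of trials under this rule, and in essentially none with chi-square throughout.

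**Step 7: does age stratification add power?** Simulation used equal age bands and placebo death rates by band of 9/9%, 6/12% or 4/14% (assumptions). Power was 30.2–30.6% for Cochran-Mantel-Haenszel and 29.9–31.2% for the unstratified chi-square. Under the null the stratified test rejected in 4.7–5.0% of trials.

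**The case against.** The strongest reply is that the below-5 convention for chi-square is usually an expected-count rule. Read that way, the switch is rare at 9% mortality and costs almost nothing, and the article may simply have shortened fuller wording. A reader might infer that the text makes observed counts the trigger, so that the switch happens in half of trials. The document does not support that: it names neither kind of count, and the 54% holds only on one reading, near 9% mortality, with the odds ratio of 2.3 carried over to death. What remains is that a rule is stated, its key term is open, and the two readings give switch rates of 54% and 8%.

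A reader might also infer that leaving out age costs power. Step 7 shows no measurable gain from stratifying; the loss comes entirely from Fisher's conservatism. Other further-efficacy tests name no age term either, so the case for age is consistency only.

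Nor can one infer a false-positive problem: the switch rule rejects in 4.8% of trials under the null at 9% mortality. The endpoint is exploratory, its power is about 31% even without a switch, and a log-rank test of survival is planned as well. All of this stands and limits the weight of the point.

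**Conclusion.** The point holds as a minor one. The trigger is not defined, and the mortality test does not use the age bands that the primary and secondary models carry. On the observed-count reading, at the plan's own 9% placebo level, power falls by about 6 points (31.3% to 25.3%) and the p value can contradict the interval. On the expected-count reading the loss is about 0.5 point. The size depends on reading eGOS level 1 as death, on the odds ratio of 2.3 applying to death, on 110 patients per arm and on the placebo death rate: the observed-count loss is negligible from about 15% mortality. The contradiction between p value and interval also assumes a Wald interval. Neither the primary analysis nor control of type I error is affected.

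**What to change.** Replace the two sentences on the mortality test with one pre-specified method: a Cochran-Mantel-Haenszel test stratified by age band (18–39, 40–60), reported with a risk difference stratified in the same way and its 95% confidence interval, so that test and estimate match. Give the reason for age as consistency with the randomisation and the other models. If a switch to Fisher's test is kept, write that it applies when an expected cell count is below 5. The cost is one or two sentences, settled before unblinding, with no new data and no effect on the sample size or any other analysis.

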## Methods/design

### Trial design

NOSTRA-III is a multi-centre, prospective, parallel-group (two groups), blinded, placebo-controlled, randomised, phase III trial of Ronopterin administration to adults with TBI of moderate or greater severity requiring intensive care. The primary objective of this trial is to demonstrate that the eGOS 6 months after injury is improved following administration of Ronopterin compared to a placebo control. Exploratory secondary and adjusted multivariable analyses will also be conducted.

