### Statistical analysis

The null hypothesis of no shift across the eight ordered categories of eGOS for the two treatment groups will be tested based on a proportional odds model stratified by age (18–39 years and 40–60 years). The treatment effect will be estimated using ordinal logistic regression as the (proportional) odds ratio of Ronopterin versus placebo with a two-sided Wald 95% confidence interval. Treatment and age (18–39 years and 40–60 years) will be included in the model. The proportional odds assumption will be tested using the chi-square score test. If the proportional odds assumption is not be fulfilled then the individual cumulative odds ratios will be presented with their 95%-confidence intervals.

The interim analysis is to be conducted after half the patients have completed their 6-month assessment (110 patients in the FAS). The proportional odds model stratified by age is used to compare the groups and the associated *p* value, *p*_1_
*p*_1_ is calculated. If the study continues to the end, the proportional odds model stratified by age based on data from patients randomised in the second stage is used to compare the groups and the associated *p* value, *p*_2_ is calculated. According to Bauer and Koehne [14] and Lehmacher and Wassmer [15], the *p* values are combined to control the type I error. If *p*(*p*_1_*p*_2_) is < 0.025, then significance can be claimed.

The efficacy of Ronopterin will be considered to be proven if the null hypothesis for the primary endpoint is rejected and if the treatment difference is in favour of Ronopterin in the sense of a shift to higher eGOS categories under Ronopterin.

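### The primary model adjusts only for two age groups and leaves out a baseline score for 6-month outcome that the trial already computes; adding the score is a cheap gain in efficiency

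*Protocol article*

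**What the plan says.** All references are to the Protocol article.

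- **Statistical analysis** fixes the confirmatory model. The null hypothesis is "tested based on a proportional odds model stratified by age (18–39 years and 40–60 years"), and the estimation model is equally explicit: "Treatment and age (18–39 years and 40–60 years) will be included in the model". The same age-stratified model gives the p value of each stage, p1 and p2.
- **Further efficacy analysis** describes a published prognostic factor that "predicts the probability of 6-month mortality or probability of 6-month unfavorable outcome". It then states: "The prognostic factor will be analysed using the *t* test with a two-sided alpha level of 0.05". The mean difference and its confidence interval "will be summarized for comparability at baseline".
- **Secondary outcomes and pre-specified covariates** lists the prognostic factor as the last of the further efficacy endpoints. Despite the heading, no entry there is identified as a covariate.
- **Trial design** adds: "Exploratory secondary and adjusted multivariable analyses will also be conducted". The covariates are not named.
- **Randomisation** stratifies by site and by the two age groups, and by no measure of injury severity.
- **Sample size and power** uses an unadjusted Wilcoxon test: "an odds ratio of 2.3 was assumed", with 220 evaluable patients and 92.2% power. It gives 80% power for an odds ratio of 2.0.

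**The concern.** A score that predicts 6-month mortality or unfavourable outcome should be closely related to 6-month eGOS, so it is the natural covariate for the primary model. The plan does two other things with it.

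First, it tests the score between randomised arms. Any baseline difference after randomisation arises by chance, so the test addresses a null hypothesis that is true by design. It neither recovers precision nor corrects an imbalance. Second, the plan files the score under efficacy endpoints, although a quantity fixed before treatment cannot show efficacy.

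Two things are at stake. One is power, mainly if the true effect is nearer 2.0 than 2.3; the article itself warns in Sample size and power that early infusion stops and missing eGOS values may dilute the effect. The other is the interim decision. **Data monitoring and interim analyses** lets the effect estimated in 110 patients guide a sample size increase to at most 330, and futility is among the possible recommendations. Chance imbalance in prognosis feeds straight into that estimate.

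**Working it through.** **Step 1. Reproduce the plan's power.** Inputs from Sample size and power: placebo eGOS distribution 0.09, 0.1, 0.1, 0.15, 0.3, 0.25, 0.005, 0.005 (sum 1); odds ratio (OR) 2.3; N = 220, 1:1; two-sided alpha 0.05.

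Under proportional odds each cumulative placebo odds is divided by the OR. At 2.3 the Ronopterin arm becomes 0.041, 0.051, 0.058, 0.104, 0.298, 0.424, 0.011, 0.011. With p̄ the average of the two arms, Σp̄³ = 0.0684.

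- Tie-corrected Wilcoxon: P(Ronopterin better, ties counted half) = 0.6265. z = 0.1265 / √[(1 − 0.0684)/12 × 2/110] = 3.37. Power = Φ(3.37 − 1.96) = 92.0%.
- Whitehead formula: V = (220/12)(1 − 0.0684) = 17.08. Power = Φ(ln 2.3 × √17.08 − 1.96) = Φ(0.833 × 4.133 − 1.96) = Φ(1.48) = 93.1%.
- Simulated Wilcoxon test, 20,000 runs: 92.6%.

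The stated 92.2% holds. At OR 2.0 the three methods give 80.7%, 81.9% and 81.4% against the stated 80%. Recruitment also agrees: 220/0.95 = 231.6, so 232.

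**Step 2. Power of the planned model with and without the score.** The score's strength is an assumption, expressed as the share of latent outcome variance it explains (R² = s²/(s² + π²/3), where s is the slope per SD of the score). The placebo distribution and the marginal OR were held at the stated values. Both models contained the age split, whose underlying variable was assumed to correlate with the score at −0.4. N = 220, Wald test, 1,000 runs per case, simulation error about 1 point.

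| Marginal OR | R² | Conditional OR | Age only | Age + score | Gain (points) |
|---|---|---|---|---|---|
| 2.0 | 0.07 | 2.07 | 82.4% | 84.8% | 2.4 |
| 2.0 | 0.20 | 2.21 | 82.7% | 90.3% | 7.6 |
| 2.0 | 0.34 | 2.40 | 81.6% | 94.7% | 13.1 |
| 2.3 | 0.07 | 2.42 | 93.8% | 94.8% | 1.0 |
| 2.3 | 0.20 | 2.59 | 92.3% | 96.4% | 4.1 |

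A second simulation, 2,000 runs per case with age left out of both models, gave:

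- OR 2.0: 83 to 84% (R² 5%), 81 to 86% (10%), 82 to 90% (20%), 82 to 93% (30%).
- OR 2.3: 93 to 95%, 95%, 97% and 98% for the same R² values.
- No treatment effect, R² 20%: two-sided rejection 4.7% without and 4.9% with the score, so no sign of inflation.

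Taken together, the gains are about 1 to 5 points at OR 2.3 and about 1 to 13 at OR 2.0. The 13 comes from R² = 0.34; at 30% the gain is 11.

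**Step 3. Check by hand.** At marginal OR 2.0, Σp̄³ = 0.0646, so V = (220/12)(1 − 0.0646) = 17.15 and √V = 4.141. Marginal: Φ(0.693 × 4.141 − 1.96) = Φ(0.91) = 81.9%. With the conditional OR 2.21 for R² 0.20: Φ(0.793 × 4.141 − 1.96) = Φ(1.32) = 90.7%. This agrees with the simulated 82.7% and 90.3%.

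**Step 4. Chance imbalance at the interim.** With 110 patients, about 55 per arm, the SD of the difference in a standardised score is √(2/55) = 0.19. At R² 0.20 the slope is √(0.25 × 3.29) = 0.91 per SD. A one-SD imbalance therefore moves the log OR by about 0.91 × 0.19 = 0.17, against ln 2.0 = 0.69: about a quarter of the effect.

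**The case against.** The planned analysis is sound as it stands. Adjusting for the age stratum gives a valid test, the power figure is right, and at the design effect the gain is only a few points on a power already above 92%. A reader might infer from the omitted covariate that the trial is underpowered or its odds ratio biased. The document supports neither: the power reproduces, and because odds ratios are non-collapsible the age-only model estimates a less conditional odds ratio, not a wrong one.

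Nor does the score predict exactly the primary outcome. It predicts binary outcomes, whereas the primary analysis looks for a shift over eight levels. Eligibility also narrows prognosis: it requires ICP monitoring, limits age to 18–60, and excludes, among others, bilateral fixed dilated pupils and resuscitation after injury. The upper R² values may therefore be optimistic. The calculations fix N at 220 and model neither the two-stage combination nor the sample size increase, which is itself a safeguard for power.

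Finally, the unnamed adjusted analyses may well use the score, and their details can properly sit in a document not shown. So the t test is the only stated use, not necessarily the only use. All of this stands, and it limits the size of the point. It does not remove it: the article fixes the confirmatory model in full, and exploratory adjusted analyses cannot change p1 or p2. That no stated decision hangs on the t test makes it harmless, but also easy to drop.

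**Conclusion.** The point holds as a recommended improvement in efficiency. The confirmatory test is valid and the 92.2% is correct. What is lost is precision from a baseline predictor that the trial already plans to compute. The power gains in the working depend on an assumed score strength that the document does not give. They are small at the design effect and become material only if the true odds ratio is nearer 2.0 and the score is at least moderately predictive. The benefit at the interim rests on the same assumption and covers only the imbalance that the score captures. Listing a baseline score as an efficacy endpoint, and testing it between randomised arms, should be corrected whatever the gain in power.

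**What to change.** Before any unblinded interim look:

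1. Add the baseline prognostic score, as a continuous covariate, to the age stratum in the proportional odds model that gives p1 and p2, and in the 3-month eGOS model.
2. State that the resulting odds ratio is conditional on age group and score. It will be somewhat larger than the age-only value (for example 2.21 against 2.0 at R² 0.20) and should not be read against the planning value of 2.3 without that note.
3. Impute missing score components from baseline data only, by a rule fixed in advance.
4. Report the score by arm descriptively and drop the t test.
5. Move the score from the further efficacy endpoints to the pre-specified covariates.

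The cost is wording in the protocol and analysis plan, a conditional estimand, and simple handling of missing components, whose frequency the article does not give. Timing is the real constraint: the first patient was enrolled in August 2016 and recruitment was due to finish by the end of 2019, so the change is clean only if made before the interim data are unblinded. If that point has passed, the score-adjusted model can still be specified as a sensitivity analysis, and items 4 and 5 still apply.
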